### Study design

This is a clinical quality improvement project with an embedded single-arm pilot study. Specifically, patients with obesity who desire to lose weight will be referred by their PCP to the WNP. Patients scheduled for a WNP appointment will be offered the opportunity to participate in research; we will aim to recruit 30 participants to the research arm of the study Research activities include (1) surveys at 0, 6, and 12 months; (2) optional semi-structured interview participation at 0 and 6 months; and (3) use of a text messaging program for remote weight monitoring.

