#### Clinical impact of the WNP

##### Change in weight

We will abstract weight and height data from the EHR for all WNP patients who complete a clinic visit within the first 12 months of clinical program operations. We will evaluate average weight change among WNP patients during the 12 months following their WNP appointment. We will also identify a contemporaneous cohort of patients with obesity matched by gender and approximate age (within 10 years) to WNP patients. The matched cohort will be selected from another Michigan Medicine primary care clinic located less than 1 mile from the pilot site clinic and serving a similar patient population. We will compare between-group weight change among WNP patients and the matched cohort. In addition to evaluating mean weight change, we will also evaluate achievement of ≥5% body weight loss.

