### Data analyses

#### Quantitative data analysis

Measures of central tendency (eg, proportions, means, standard deviations) will be used for all descriptive analyses. We will calculate mean 3-month and 6-month weight changes from baseline. We will also calculate the number of participants that achieve ≥5% body weight loss at 6 and 12 months. We will compare between-group changes (ie, all WNP participants versus WNP research participants and all WNP participants versus matched cohort) in weight using a difference-in-difference analytic approach. Among WNP research participants, we will also calculate mean weight change based on MPOTA-WM data. We will conduct all analyses using Stata 15.

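### WNP versus matched cohort: difference-in-difference from an undefined baseline, with no comparator index date or pre-index weights, cannot separate a referral-time weight deviation or unequal prior trends from a WNP effect

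*Protocol article*

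**What the plan says.** The end of the Background states a directional hypothesis: patients who engage in the WNP will lose more weight than a contemporaneous matched cohort from another clinic.

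The parts of the plan that bear on testing it are:

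- **Estimator** (Quantitative data analysis): between-group changes are compared "in weight using a difference-in-difference analytic approach". The same sentence covers two contrasts: all WNP versus WNP research participants, and all WNP versus matched cohort.
- **Reference point** (same section): "We will calculate mean 3-month and 6-month weight changes from baseline". Baseline is not defined further.
- **Time window** (Clinical impact of the WNP, Change in weight): "We will evaluate average weight change among WNP patients during the 12 months following their WNP appointment".
- **Data source** (same section): "We will abstract weight and height data from the EHR for all WNP patients who complete a clinic visit". No earliest date is given.
- **Entry to the WNP group** (Study design): "patients with obesity who desire to lose weight will be referred by their PCP to the WNP".
- **Comparators** (Clinical impact of the WNP, Change in weight): a "contemporaneous cohort of patients with obesity matched by gender and approximate age (within 10 years) to WNP patients", "selected from another Michigan Medicine primary care clinic located less than 1 mile from the pilot site clinic". No index date or triggering visit is given for them. Prior weight change is not a matching variable.
- **Binary outcome** (same section): "we will also evaluate achievement of ≥5% body weight loss".

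**The concern.** Difference-in-difference removes a fixed difference in level between two groups. It does not remove a temporary deviation in one group's starting value, and it does not remove a difference in slope that was present before treatment. With one reference value per patient it reduces to a comparison of two change scores, and the parallel-trends assumption cannot be examined.

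The two cohorts reach their starting value by different routes. A WNP patient's clock starts after a decision to seek weight loss and a referral. A comparator's clock starts at a time the article does not state. If people tend to seek help when they are temporarily heavier than usual, their return to usual weight appears as loss after the appointment. If they are on a sustained upward trend, the bias runs against the WNP. If they have already begun to lose weight, it runs in the WNP's favour again. Matching on gender and age addresses none of these.

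At stake are the mean weight comparison, the share reaching 5% loss, and through them the preliminary effectiveness evidence that Future directions intends to carry into a large pragmatic trial.

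**Working it through.** The article gives no SD, effect size or power calculation for the weight comparison, so there is no stated figure to reproduce. Everything below is illustrative. The only input from the document is the estimate of about 150 WNP patients in the first year (Recruitment).

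**1. What passes into the estimate.** Let the WNP and comparator baselines carry mean temporary excesses e_W and e_C that later resolve. With no true effect, the difference-in-difference shows a spurious loss of e_W − e_C. For all WNP versus WNP research participants, both groups were referred, so the two terms are similar and the difference is near zero.

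**2. How large e_W might be.** Assume a temporary deviation t ~ N(0, s²), logit P(referral) = −3 + b·t/s, and e_C = 0. The odds of referral per SD are then multiplied by e^b. Mean t among those referred, by simulation:

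| s (kg) | b=0.25 (odds ×1.3) | b=0.5 (×1.6) | b=1.0 (×2.7) |
|---|---|---|---|
| 1 | 0.24 | 0.47 | 0.86 |
| 2 | 0.47 | 0.93 | 1.73 |
| 3 | 0.71 | 1.40 | 2.59 |

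Check by approximation: the mean is about s·b·(1 − p), with p = 1/(1 + e³) = 0.047. For s = 2 and b = 0.5 this is 2 × 0.5 × 0.953 = 0.95, against 0.93 simulated. The range is about 0.2 to 2.6 kg. For an assumed 100-kg patient, 1 kg is 1 percentage point and the 5% target is 5 kg.

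**3. Effect of a wait and of incomplete resolution.** Assume the deviation decays with monthly correlation ρ. From an excess of 0.93 kg at referral, the spurious 12-month loss is 0.93(1 − ρ¹²) if baseline is taken at referral: 0.92, 0.87 and 0.67 kg for ρ = 0.7, 0.8 and 0.9. If baseline is taken two months later it is 0.93ρ²(1 − ρ¹²): 0.45, 0.55 and 0.54 kg.

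**4. Consequence for the comparison.** Assume 150 per group (1:1 matching), a two-sided 5% test and no true effect. SE = SD·√(2/150). P(reject) = Φ(e/SE − 1.96) + Φ(−e/SE − 1.96), where e is the excess in percentage points.

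| SD of % change | SE | e=0.5 | e=1 | e=2 |
|---|---|---|---|---|
| 5 | 0.58 | 14% | 41% | 93% |
| 7 | 0.81 | 9.5% | 24% | 70% |
| 9 | 1.04 | 8% | 16% | 49% |

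With SD 7 and zero mean change, the share reaching 5% loss is 1 − Φ(5/7) = 23.8%. It rises to 1 − Φ(4/7) = 28.4% for e = 1 and 1 − Φ(3/7) = 33.4% for e = 2.

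**5. Which remedies work.** Take a temporary peak with mean excess 0.93·ρ^|m| at month m from index, three-monthly weights and no true effect. The figures are for ρ = 0.7, 0.8 and 0.9.

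| Approach | Result (kg) |
|---|---|
| Change from index weight: spurious loss | 0.92, 0.87, 0.67 |
| Placebo difference, months −12 to 0: gain shown | 0.92, 0.87, 0.67 |
| Baseline = mean of months −24 to −6: spurious loss | 0.01, 0.01, −0.03 |
| Departure at month 12 from a line fitted to months −24 to 0: spurious loss | 0.80, 0.90, 0.90 |

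Worked for ρ = 0.9. The nine pre-index means average 0.359 and their least-squares slope is 18.09/540 = 0.0335 kg per month, so the line projects 0.359 + 24 × 0.0335 = 1.16 kg at month 12. The actual excess is 0.93 × 0.9¹² = 0.26 kg. The departure is 1.16 − 0.26 = 0.90 kg, larger than the 0.67 kg from simple change.

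**6. Limit of the earlier baseline.** Suppose there is no peak but a sustained extra gain of g kg per year in WNP patients. Change from index is biased against the WNP by g. A baseline centred 15 months before index is biased against it by (15 + 12)/12 × g = 2.25g. The earlier baseline is therefore an additional analysis to read with the placebo result, and not a replacement.

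**The case against.** A reader might infer that baseline is a single weight taken at the moment of seeking help, that earlier weights are excluded, that trends are never checked, and that a weight peak at referral is therefore credited to the WNP. The article does not support this. It leaves baseline undefined, sets no earliest date for extracted weights, and gives no data on weight before referral. Wanting to lose weight does not show recent gain. Detailed model specification and diagnostics also commonly sit in an analysis plan that is not shown. All of this stands, and it limits the point to what the article itself sets out: the estimator, the change window, the route of entry and the matching variables.

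The kilogram figures are constrained by nothing in the document. They set the comparator's excess to zero, although routine weights are often recorded when patients attend for care. Scheduling, a pre-visit questionnaire and prompted laboratory tests separate referral from appointment, so part of a peak could fade first (step 3). These limits also stand.

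The primary outcomes are feasibility and acceptability (Feasibility and acceptability of the WNP), so this does not threaten the pilot's main purpose. However, the Background states a comparative weight-loss hypothesis, and Limitations and opportunities mentions neither regression to the mean nor prior trends.

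**Conclusion.** The concern holds in limited form, for WNP versus matched cohort only. Followed as described, the comparison cannot distinguish a WNP effect from recovery after a temporary deviation around referral, or from different weight trends before it. Neither the sign nor the size of the bias can be stated from the document.

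If the deviation is upward, the range of 0.2-2.6 kg rests wholly on assumed SDs of 1-3 kg and assumed referral odds, and a wait before the visit would reduce it. Even a small excess matters: with 150 per group and SD 7, one percentage point raises the false-positive rate from 5% to about 24%.

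This is worth correcting before the weights are extracted, at a priority suited to a non-primary outcome. The comparison of all WNP with WNP research participants is largely unaffected.

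**What to change.** 1. Define the baseline window, and assign each comparator an index date, for example a primary care visit in the same calendar period as the matched patient's WNP appointment.
2. Extend the EHR weight extraction for both cohorts to 24 months before index.
3. Report a placebo difference-in-difference over the 12 months before index. A clear difference there shows that the cohorts were not moving in parallel.
4. Repeat the weight comparison with the mean of weights 6-24 months before index as an alternative baseline, and report it beside the comparison from index.
5. Do not make departure from a linearly extrapolated pre-index slope the main estimate. It projects a temporary rise forward and can keep or increase the bias.

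The cost is a wider date range in the same EHR query and two further analyses. Some patients will lack earlier weights, so the number contributing to each analysis should be reported by cohort.

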#### Qualitative data analysis

Semi-structured interviews will be recorded and transcribed verbatim. Interviews will be imported into qualitative analysis software, Dedoose (*
n.d.), and analyzed using template qualitative analysis (Brooks *et al*., 2015). The initial codebook will be developed to reflect interview questions, and additional codes will be subsequently generated to reflect new concepts that emerge from the data. Two trained coders will independently review and code each transcript and then meet to resolve coding differences and iteratively revise the codebook.*

#### Integrated analysis

Consistent with a mixed-methods sequential explanatory design (Ivankova, 2006), we will integrate (ie, connect) the quantitative and qualitative findings in the final stage of data analysis. In this way, we will interpret our quantitative data in the context of qualitative participant experience.

## Discussion

We describe the design, rationale, and study protocol for a quality improvement initiative with an embedded single-arm pilot study. The WNP aims to overcome the known challenges of providing evidence-based obesity management in general practice settings. This model consists of three components that have demonstrated effectiveness when used independently for other primary care improvement efforts: (1) team-based collaborative care; (2) personalized weight management plans; and (3) population health management to optimize patients’ outcomes.

### Limitations and opportunities

This program has several potential limitations. First, it will be implemented at a single site and thus may not be generalizable to all practice settings. However, we believe the WNP model offers a conceptual and practical framework that may be successfully adapted to diverse primary settings where at least one physician is certified in obesity medicine. Second, cost barriers may impede patients’ use of certain weight management resources. Fortunately, there is growing insurance coverage for weight management services (Jannah *et al.*, 2018), drug discount programs support the use of some anti-obesity medications (Prescription Prices, Coupons & Pharmacy Information – GoodRx, n.d.), and most health plans cover nutrition counseling services. Moreover, we will utilize low-cost, community-based resources such as Diabetes Prevention Programs when developing personalized obesity treatment plans. Fourth, some components of the current WNP model (eg, MPOTA-WM outreach) require research funding, which may limit implementation in general practice settings. However, to the extent possible, the WNP model uses billable services, and we will aim to identify opportunities to integrate MPOTA-WM into routine clinical care. Moreover, remote monitoring tools are now common features of many EHR systems, reimbursement guidelines encourage use of such tools (Final Policy, Payment, and Quality Provisions Changes to the Medicare Physician Fee Schedule for Calendar Year 2021 | CMS, (n.d.), and additional policy changes on the horizon may enable more providers to play active roles supporting patients with obesity (Cassidy, 2019).

### Future directions

We plan to evaluate the pilot WNP using mixed quantitative and qualitative data collection methods. These data will enable us to evaluate the program’s feasibility, acceptability, and preliminary weight loss effectiveness. Moreover, we will use qualitative data obtained during interviews with patients to identify the features of the program that work well and those that could be improved. These data will enable us to refine the program and test its effectiveness in diverse practice settings. We anticipate evaluating the refined program in a future large-scale pragmatic trial using an effectiveness-implementation hybrid type 1 design to evaluate the program’s weight loss effectiveness at 12 and 24 months while also gathering information on implementation processes and determinants (Curran *et al.*, 2012).

## Conclusions

Obesity is a complex chronic condition that demands evidence-based, personalized, and longitudinal care. To deliver such care in general practice, the WNP leverages ABOM Diplomate expertise, health system and community weight management resources, and EHR-based population health management tools. Moreover, to the extent possible, the WNP uses existing weight management resources and billable services to help patients develop personalized weight management plans. Thus, the model may provide an effective, sustainable, and scalable opportunity to improve obesity management in primary care settings.
